#### **10.5 Clinical Symptoms of Chronic Pulmonary Disease Exacerbation**

Clinical symptoms of chronic pulmonary disease exacerbation will be assessed on Day 7 ± 2 days, Day 56 ± 7 days, Day 112 ± 7 days, and Day 168 ± 7 days (APPENDIX 1. Study Procedure Schedule).

Clinical symptoms of chronic pulmonary disease exacerbation that require therapy with antibiotics in CF patients include the presence of at least 4 out of 12 possible signs or symptoms [24]:

1. Change in the color or amount of sputum
2. Blood expectoration or its aggravation
3. Cough aggravation
4. Dyspnea aggravation
5. Aggravated malaise, fatigue, or atony
6. Temperature above 38°C
7. Anorexia or weight loss
8. Pain or tenderness of nasal sinuses
9. Changed nature of nasal discharge
10. Abnormalities in the chest exam
11. Pulmonary function impairment by 10% or more
12. Radiographic changes

In the case of bronchopulmonary disease exacerbation, the indications for antibiotic therapy, selection and dose of the medicinal product, and therapy duration should be determined by the clinical investigator. The criteria for discontinuation of the antibiotic therapy should be a reversion of basic clinical symptoms of bronchopulmonary disease exacerbation to the level that is a baseline one for this patient. Microbiological analysis of sputum and chest X-ray examination will be performed if required, by the decision of the clinical investigator.

In this study, all cases of chronic pulmonary disease exacerbation will be considered as adverse events of special interest.

## **10.6 Telephone Call**

On Day 28  $\pm$  3 days (Week 4), Day 84  $\pm$  7 days (Week 12), and Day 140  $\pm$  7 days (Week 20), the clinical investigator or employees of the study center authorized by him/her will contact every patient via telephone and ask questions about the state of health, concomitant treatment, medicinal product administration compliance to make sure that all necessary information, including adverse events (AEs) is recorded in the Patient Diary.

To assess clinical symptoms of chronic pulmonary disease exacerbation, the clinical investigator or an employee of the study center authorized by him/her will ask the patient the following questions:

- Do you notice any change in the cough?
- Do you suffer from night cough?
- Do you notice blood in sputum?
- Do you notice the increased volume of sputum and a change in its nature?
- Do you feel that dyspnea is worsening?
- Do you notice a fever or increased heart rate?
- Do you notice poor appetite?
- Do you notice weight loss?
- Do you feel increased fatigue at exertion?

If positive answers are given to these questions, then by the decision of the clinical investigator the patient may be invited to an unscheduled visit to the study center.

## **10.7 Electrocardiography**

A standard 12-lead ECG is performed.

The patient should rest for at least 5 minutes prior to the ECG recording and should be resting during the recording.

ECG is performed at the Screening and on Day  $168 \pm 7$  days during treatment, according to the Study Procedure Schedule (APPENDIX 1. Study Procedure Schedule). General interpretation of ECG should be performed by a certified specialist. The date of ECG registration, patient's surname, and general ECG conclusion should be indicated.

Parameters subject to mandatory recording are the heart rate (HR) and RR, PQ, QRS, and QT intervals. The corrected QTc interval is calculated using Bazett's formula:

$$QTc = QT/\sqrt{(RR(s))},$$

ECG records should be kept in the patient's medical records. The report must include information about whether the ECG is normal, or about the presence of clinically significant or clinically insignificant changes.

If ECG performed during the study reveals any changes that the Investigator considers as clinically significant, the patient, if necessary, should undergo other diagnostic tests in accordance with the local practice and receive appropriate treatment.

## **10.8 Spirometry**

Pulmonary function test (spirometry) will be performed according to the Study Procedure Schedule (APPENDIX 1. Study Procedure Schedule) at the Screening Visit, on Day  $7 \pm 2$  days, Day  $56 \pm 7$  days, Day  $112 \pm 7$  days, and Day  $168 \pm 7$  days in accordance with the standard procedure described in the Guidelines for Conducting of Spirometry.

The quality of spirometry results obtained at the Screening Visit will be assessed centrally by a certified functional diagnostics specialist who has no access to the patient's personal data, medical history, or information on clinical manifestations of the disease. The results of the spirometry performed at the Screening, centrally assessed, and approved, will be used as baseline values.

## **10.9 DNase Concentration Assessment**

The sputum DNase assessment of the patients who have agreed to participate in an additional study to assess the pharmacokinetics of the product will be performed once prior to the first inhalation and twice after the first inhalation of the study/reference product.

**Sputum samples** will be collected 1 hour  $\pm$  15 min before the inhalation of the study/reference product (*after the patient's randomization*), then 15 min  $\pm$  5 min and 1 hour 45 min  $\pm$  15 min after the end of inhalation (APPENDIX 1. Study Procedure Schedule).

Based on the individual data on DNase concentrations in sputum at each time point, following pharmacokinetic (PK) parameters will be calculated:

- $C_{\max}$  = maximum DNase concentration
- $T_{\max}$  = time to maximum DNase concentration

If necessary, other parameters may be calculated.

The assessment of DNase concentration in the sputum of the patients will be carried out in the specialized analytic laboratory. The procedure for collection, storage, and transportation of the sputum samples will be described in the laboratory guidelines that will be provided to the study centers. All essential data about biosample collection should be properly documented.

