## 1.3 Preclinical and Clinical Study Results

### 1.3.1 Preclinical Safety Data

#### 1.3.1.1 Pharmacokinetics and Metabolism in Animals

##### *Absorption*

The study of systemic absorption of the original medicinal product after administration by inhalation in rats and human primates has found that the medicinal product has a low systemic absorption (less than 15% in rats and less than 2% in primates).

After the aerosol inhalation with a concentration of 10 µg/L for 13–15 min (the average particle diameter of aerosol was 3–4 µm) the rodents received the dose of 0.15 mg/kg (dose for the lower respiratory tract). DNase was found in the lungs immediately after the administration in concentrations 3.04 to 1.93 µg/lungs and 0.65 to 0.1 µg/lungs after 24 hours.

The product absorption after oral administration in rats was insignificant. After a single oral administration of the medicinal product at a dose of 10 mg/kg to rats, the serum samples were collected after 48 hours. The product concentration was lower or slightly higher than the lower limit of quantification (2 ng/mL). [58]

Changes in concentrations of the medicinal products dornase alfa (GENERIUM JSC) and Pulmozyme® (F. Hoffman-La Roche, Switzerland) in the lung tissues and in the blood serum of rats were assessed in the comparative study of subchronic toxicity following inhalation at a dose of 0.2 mg/kg for 28 days. No significant difference was found between the medicinal products dornase alfa (GENERIUM JSC) and Pulmozyme® (F. Hoffman-La Roche, Switzerland), as well as no difference in groups of females and males.

Toxicokinetics of dornase alfa (GENERIUM JSC) and Pulmozyme® (F. Hoffman-La Roche, Switzerland) in rats at the studied doses is comparable. [13]

The pharmacokinetics of the medicinal product in primates was studied with the inhaled concentrations of 0.39 mg/kg, 1.23 mg/kg, and 5.65 mg/kg. No product concentration in the blood serum was recorded (lower than 2 ng/mL) within 312 hours after the inhalation at a minimum dose. A measurable minimum product concentration was found in the serum after 1.23 mg/kg and 5.65 mg/kg inhalation. The maximum recorded concentration was lower than 40 ng/mL and AUC was 765 and 1,387 h/mL for the dose of 5.65 mg/kg. The medicinal product inhalation are suggested to have its low systemic availability. Its bioavailability for rats was 15%, and for monkeys less than 2%.

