#### *Elimination*

After intravenous administration in rats and primates, the elimination half-life of the medicinal product is 3 to 4 hours. Studies in rats indicate that, following aerosol administration the

disappearance half-life of dornase alfa from the lungs is 11 hours. [42, 58] In intravenous administration, the total clearance was between 17.6 and 58 mL/kg\*h, in most tests the medicinal product was eliminated from the circulatory system in 24 hours. The volume of product distribution was approximately equal to the plasma volume (50–60 mL/kg). [68]

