The data on the original medicinal product Pulmozyme® were used to determine effective doses of the investigational product Tigerase as therapy for cystic fibrosis as well as the medicinal product administration schedule. In accordance with the instructions for medical use of the original medicinal product, Pulmozyme® (dornase alfa) is used once a day at a dose of 2.5 mg (the contents of one ampoule) by inhalation without dilution, using a jet nebulizer. Dornase alfa should not be diluted or mixed with other products or solutions in the jet nebulizer cup. Mixing the product with other medicinal products (MPs) can lead to undesirable structural and/or functional changes in dornase alfa.

Therefore, for the purposes of the clinical study to assess safety and efficacy in patients with cystic fibrosis, the investigational product Tigerase (GENERIUM JSC, Russia) and reference product Pulmozyme® (F. Hoffman-La Roche, Switzerland) will be inhaled once a day at a dose of 2.5 mg (1 ampoule contains 2.5 mg of active ingredient) for 24 weeks  $\pm$  1 week.

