If a patient meets all inclusion/exclusion criteria, he/she will be invited to the study center to undergo the randomization and start the study therapy (Visit 2. Day 1). In this case, the patient will be warned that prior to his/her visit to the study center at Day 1 (Visit 2) he/she should not use Pulmozyme® that is administered as part of the standard medical service.

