## 9 TREATMENT PERIOD

### 9.1 Visit 2. Day 1. Randomization (Week 0)

A procedure of randomization will be performed at Visit 2. A unique randomization number will be assigned to each patient. Group I patients will receive the investigational product Tigerase, Group II patients — the reference product Pulmozyme®.

During participation in the study, the patients receiving Pulmozyme® as part of their standard medical service will be provided by the Sponsor with either investigational product Tigerase or reference product Pulmozyme® according to the randomization results.

At Visit 2, the following study procedures will be carried out:

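### Day 1 sputum Cmax is not corrected for the pre-dose level, so in patients already on Pulmozyme it can include residual comparator, and an uncorrected Cmax comparison can be drawn toward equality

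*Protocol*

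**What the plan says.** - **Sampling.** Section 10.9 takes sputum "once prior to the first inhalation and twice after the first inhalation of the study/reference product". Sections 9.1 and 10.9 put the three samples at 1 h before the Day 1 inhalation, and at 15 min and 1 h 45 min after its end. No PK sample is taken later.
- **Prior users.** Section 4.2 does not exclude prior dornase alfa. Section 9.1 provides for patients on Pulmozyme who, "as part of their standard medical service will be provided by the Sponsor with either investigational product Tigerase or reference product" Pulmozyme, depending on the randomisation.
- **Stopping own supply.** Section 8.2 warns the patient that "prior to his/her visit to the study center at Day 1 (Visit 2) he/she should not use Pulmozyme". It does not say from when.
- **Parameter and analysis.** Sections 10.9 and 12.1 define Cmax only as the maximum DNase concentration. Section 15.1 plans descriptive statistics and, if necessary, a Mann–Whitney test. It admits to the PK population any patient with data at one or more sampling times.
- **Precedent.** Section 1.3.2 reports that the phase I study analysed plasma DNase both as a total and net of the pre-treatment level.

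**The concern.** Both products are dornase alfa and the measured quantity is DNase concentration, so the result does not show which product a molecule came from. In a patient who used Pulmozyme the day before, the Day 1 value is the new dose plus whatever remains of the old one. In the Tigerase arm that remainder is the comparator.

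Both arms carry the same expected remainder. Adding the same amount to both sides of a ratio moves it toward 1. The synopsis states objective 5 as a comparison of sputum DNase between the products (section 2 words it as an evaluation). In a biosimilar programme, an artefact toward similarity is the direction that most needs to be ruled out.

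**Working it through.** The protocol gives no sample-size basis, margin or expected ratio for the PK part, so there is no PK design figure to reproduce. The check asks how large the carry-over could be on the protocol's own data.

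**Inputs**
- Lung half-life in rats, 1.3.1.1 (Elimination): "disappearance half-life of dornase alfa from the lungs is 11 hours".
- Rodent lung content, 1.3.1.1 (Absorption): 3.04 to 1.93 µg/lungs immediately after dosing, then "0.65 to 0.1 µg/lungs after 24 hours".
- Background schedule, 1.5: Pulmozyme "is used once a day at a dose of 2.5 mg". If only the Day 1 dose is skipped, the gap is about 24 h.
- Assumptions: human sputum clearance lies within the animal range (no human sputum half-life is given), and the true Tigerase/Pulmozyme Cmax ratio is R = 0.70. The share of prior users is not stated.

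**Step 1: half-life cross-check.** t½ = 24·ln 2 / ln(C0/C24).
- 3.04 to 0.65: 16.64 / 1.543 = 10.8 h, in line with the stated 11 h.
- 1.93 to 0.10: 16.64 / 2.960 = 5.6 h.

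The protocol does not say which values of the two ranges belong together, so 5.6 h and 11 h are carried as a range.

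**Step 2: residual in a daily user**, as a fraction of one dose's peak: r = 0.5^(gap/t½) / (1 − 0.5^(24/t½)).
- 11 h, 24 h gap: 0.2204 / 0.7796 = 0.283.
- 5.6 h, 24 h gap: 0.0513 / 0.9487 = 0.054.
- Assumed 2 h, 24 h gap: 0.0002, effectively nil.

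**Step 3: uncorrected ratio** = (R + r)/(1 + r).
- 11 h: 0.983 / 1.283 = 0.77. The share of the relative difference lost is r/(1 + r) = 0.22.
- 5.6 h: 0.754 / 1.054 = 0.72 (share lost 0.05).
- 11 h with half the patients prior users (mean residual 0.141): 0.841 / 1.141 = 0.74.
- 11 h with a 72 h gap: r = 0.0137, ratio 0.704. This only shows that the size depends on the interval that 8.2 leaves open.

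**Step 4: mean absolute difference.** (R + r) − (1 + r) = R − 1, whatever r is. A simulation with 12 per arm and R = 0.5 gave −0.50 with and without the residual.

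**Step 5: rank test.** In the same simulation (log-normal values, R = 0.5, every patient carrying a mean residual of 0.283), Mann–Whitney power fell from 0.87 to 0.81 at an assumed log-SD of 0.5, and from 0.49 to 0.38 at 0.8.

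**Step 6: what subtraction would do.** At 11 h, the residual decays between the pre-dose sample and the first post-dose sample (about 1.25 h, ignoring inhalation time) by the factor 0.5^(1.25/11) = 0.924. Subtracting the full pre-dose value therefore over-corrects by 0.076 × 0.283 = 0.021. The corrected ratio is (0.70 − 0.021)/(1 − 0.021) = 0.69, against 0.77 uncorrected.

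**The case against.** The strongest reply is that the plan already collects what is needed. The sample taken 1 h before the first inhalation, in both arms, measures residual drug plus endogenous DNase in each patient. Section 10.9 allows further parameters, phase I used a baseline-subtracted analysis, and a statistical analysis plan (not shown) could specify the same here. This largely stands: the carry-over is observable and correctable. But the protocol itself fixes the Cmax definition and the PK analysis, neither mentions a correction, and section 15.1 would admit a patient who has no pre-dose sample, or only that one.

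Four limits also stand.
- The comparison is descriptive, with an optional test and no equivalence criterion.
- The magnitude rests on rodent whole-lung content, not on sputum from patients with cystic fibrosis.
- Only prior users are affected.
- Prior users can be identified from the treatment history (10.1) and the concomitant-therapy record (7.1), although neither section asks for the time of the last dose.

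A reader might infer more than this, in three ways.
- *That there is no stop of prior Pulmozyme at all.* Section 8.2 does tell patients not to use it before Day 1. What is missing is the interval.
- *That the PK comparison as a whole is biased in the sponsor's favour.* Step 4 shows that the mean absolute difference is not, and no decision rule uses the ratio.
- *That an uneven share of prior users adds to the bias.* With 12 per arm and half the patients prior users, the imbalance has SD √(2 × 0.5 × 0.5/12) = 0.20. Times 0.28, that is about 0.06 of a peak. This is random error in either direction, not a pull toward equality.

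**Conclusion.** The point holds in a limited form. Followed as written, the protocol yields a Cmax that in prior Pulmozyme users can contain comparator drug, and an uncorrected ratio or rank comparison can be drawn toward equality. With a 24 h gap and the rat lung data taken as an assumption, a true 0.70 would be seen in prior users as about 0.72 to 0.77, so between about a twentieth and a fifth of the relative difference is lost. With half the patients prior users, the upper figure is about 0.74. With faster human clearance or a longer gap, there is little or no effect.

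The documents do not support calling the PK result invalid or requiring a different sampling day. The pre-dose sample is already planned and no formal conclusion depends on the ratio. The point is still worth acting on, because the remedy costs almost nothing and the comparison is between a biosimilar and its reference product.

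**What to change.** 1. In 10.9, 12.1 and 15.1, define Cmax from the post-dose samples net of the patient's own pre-dose concentration, as was done in phase I, or use the pre-dose concentration as a covariate. Report the uncorrected Cmax alongside.
2. In 15.1, require the pre-dose sample and at least one post-dose sample for the PK comparison.
3. Record the date and time of the last dornase inhalation before Day 1.
4. Reconcile 8.2 with 9.1 and 10.9 so that the period without own Pulmozyme before Day 1 has only one reading. No interval is proposed here.

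The cost is a wording amendment and one added data item, with no extra samples or visits.

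Moving the three samples to Visit 3 (Day 7 ± 2) is an option, since any residual drug would by then be almost entirely the assigned product. The price is a steady-state rather than first-dose comparison, loss of the only sample taken before study drug (and with it the view of endogenous DNase), and dependence on unsupervised home dosing in the preceding days.

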## **10.10 Sweat Test**

The sweat test using the biochemical method (chloride assay in the sweat gland secretion) or sweat test (semi-quantification of sweat chlorides or quantification of sweat electrolytes) will be performed to the patients at the Screening Visit *in the absence of documented confirmation of the cystic fibrosis diagnosis*.

## **10.11 DNA Probe Assay**

DNA probe assay will be performed at the Screening to detect mutations of the cystic fibrosis transmembrane regulator (CFTR) in patients *in the absence of documented confirmation of the cystic fibrosis diagnosis*.

## **10.12 Laboratory Tests**

Blood sampling for complete blood count and biochemistry is carried out on an empty stomach before the administration of the study/reference product.

### **10.12.1 Complete Blood Count**

For complete blood count, a venous blood sample will be collected at the Screening, during treatment on Day  $56 \pm 7$  days and Day  $168 \pm 7$  days in accordance with both the Study Procedure Schedule (APPENDIX 1. Study Procedure Schedule) and the standard laboratory procedure of the clinical center.

**The following parameters are assessed:**

- Hematocrit (HCT)
- Hemoglobin (Hb)
- RBC count
- Platelet count
- Erythrocyte sedimentation rate (ESR)
- Leukocyte count

**WBC differential:**

- Neutrophils (%)
- Eosinophils (%)
- Basophils (%)
- Monocytes (%)
- Lymphocytes (%)

**10.12.2 Biochemistry**

**A biochemistry test** is performed at the Screening, during treatment on Day  $56 \pm 7$  days and Day  $168 \pm 7$  days in accordance with both the Study Procedure Schedule (APPENDIX 1. Study Procedure Schedule), and the standard laboratory procedure of the clinical center.

**The following parameters are assessed:**

- Total protein
- Glucose
- Total bilirubin
- Urea
- Creatinine
- Alanine aminotransferase (ALT)
- Aspartate aminotransferase (AST)

**10.12.3 Serological Tests**

- Hepatitis B surface antigen (qualitative test for hepatitis B surface antigen, HBsAg)
- Hepatitis C antigen antibodies (qualitative test for the total anti-HCV)
- Human immunodeficiency virus (HIV1 and HIV2) antibodies (qualitative test for anti-HIV1 and anti-HIV2)

Serological tests are performed on an empty stomach in accordance with the Guidelines for Conducting Laboratory Tests at the Screening for the exclusion of patients with positive test results. Suitable test results should be received not later than 30 days before the Screening Visit.

#### **10.12.4 Assay of Anti-Drug Antibodies, Including Production of Neutralizing Antibodies**

Assay of anti-drug antibodies (IgG, IgE), including the production of neutralizing antibodies to the study/reference product, will be performed at the analytical laboratory.

Blood samples will be collected on an empty stomach at the Screening Visit, on Day  $56 \pm 7$  days and Day  $168 \pm 7$  days.

#### **10.12.5 Urine Express Pregnancy Test**

Women with preserved childbearing potential (those who have not been surgically sterilized) will undergo a urine test for chorionic gonadotropin with a test-strip ( $\beta$ -hCG) during the Screening Visit, on Day  $56 \pm 7$  days and Day  $168 \pm 7$  days.

Before the treatment initiation, women with preserved childbearing potential should agree to use of reliable contraception methods throughout the study (sexual abstinence or any combination of the following two methods: male or female condom with spermicide, intrauterine device (IUD), diaphragm with spermicide, contraceptive sponge, cervical cap with spermicide).

#### **10.12.6 Urinalysis**

Urinalysis (UA) will be performed in accordance with the standard laboratory practice of the clinical center. UA will be performed at the Screening, during treatment on Day  $168 \pm 7$  days in accordance with the Study Procedure Schedule (APPENDIX 1. Study Procedure Schedule).

**The following parameters are assessed:**

- General properties: specific gravity, pH, protein, glucose, bilirubin, urobilinogen, ketone bodies, nitrites, erythrocytes
- Urinary sediment microscopy: epithelial cells, erythrocytes, leukocytes, cylinders, bacteria, salts

#### **10.12.7 Receipt, Preparation, Storage, and Shipment of Biological Samples**

Collection, storage, and transportation of biological samples for laboratory tests should be performed according to requirements and recommendations of the Guidelines for Conducting Laboratory Tests using laboratory kits provided by the Sponsor as part of this study. All essential data about biosample collection should be properly documented.

